**Figure 1 F1:**
[figure not shown]
**Spending functions for alpha or type I error (on left vertical axis) and beta or type II error (on right vertical axis) as a function of information time on horizontal axis, where information time is the proportion of the maximum planned sample size available for a particular interim analysis. **Lines represent the cumulative error spent throughout the trial. Beta is spent faster than alpha to allow the study to stop early more readily for futility than for efficacy. Lines are continuous, allowing flexibility in choice of monitoring times, but interim monitoring will only be done at the pre-specified times for this study.

**Figure 2 F2:**
[figure not shown]
**Stopping boundaries for efficacy and futility. Plot of the standardized treatment effect (z- statistic) on vertical axis and accrued sample size on the horizontal axis, where a z-statistic of zero indicates no treatment effect. **Outside shaded regions indicate sufficient evidence to reject null hypothesis for efficacy (top) or harm (below), while inside shaded region indicates evidence to stop for futility, or no effect.

#### Adaptive Design Option

At the third planned group sequential analysis (N = 728 patients), an adaptive sample size extension of the trial may be proposed to study one or more of the interventions that showed a modest but important treatment effect but had not yet crossed an efficacy (or futility) boundary. The method of Muller and Schafer[47] would be used to the extent that intervention with an increased sample size in a second stage while preserving the overall Type I error of the study. A second stage with new stopping boundaries would be designed with sample size and planned interim analyses to be able to detect a revised treatment effect with the desired power. Results from the 1^st ^and 2^nd ^stages for that intervention would be combined in a final analysis. East and SAS statistical software will be used for the sample size calculations, interim analyses and final analyses.

### Sample size considerations

We estimate that 25% of patients receiving no intervention (i.e., the control) will have at least one major complication. We further hypothesize that all interventions will not have the same effect and will power the study for a relative reduction of 40% or more for at least one intervention, and 20% and 10% versus respective controls for the other two. Our design will thus require a maximum of 970 total patients for the original group sequential portion of the study to have 90% power at the 0.05 significance level to detect a 40% reduction on the primary outcome for the most promising intervention.

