**Methods/Design:**

The DeLiT Trial is a factorial randomized single-center trial of dexamethasone vs placebo, intraoperative tight vs. conventional glucose control, and light vs deep anesthesia in patients undergoing major non-cardiac surgery. Anesthetic depth will be estimated with Bispectral Index (BIS) monitoring (Aspect medical, Newton, MA). The primary outcome is a composite of major postoperative morbidity including myocardial infarction, stroke, sepsis, and 30-day mortality. C-reactive protein, a measure of the inflammatory response, will be evaluated as a secondary outcome. One-year all-cause mortality as well as post-operative delirium will be additional secondary outcomes. We will enroll up to 970 patients which will provide 90% power to detect a 40% reduction in the primary outcome, including interim analyses for efficacy and futility at 25%, 50% and 75% enrollment.

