### Interim Monitoring Plan and Adaptive Design Options

The first stage of the study will be a traditional (i.e., non-adaptive) group sequential design[44,45], where interim analyses for both efficacy and futility will be conducted after 25%, 50% and 75% of the patients have been enrolled, and at the end of planned enrollment, as needed. Interventions with either a large or very small treatment effect will likely cross boundaries for efficacy or futility, respectively, at one of the interim analyses, and be stopped early. By the final analysis (including a possible adaptive stage, as explained below), all of the interventions will have either crossed an efficacy or futility boundary.

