## Discussion

A factorial design will enable us to simultaneously study the effects of the three interventions; dexamethasone vs placebo, intraoperative tight vs. conventional glucose control, and light vs deep anesthesia, in the same population, both individually and in different combinations. Such a design is an economically efficient way to study the three interventions in one clinical trial vs three, especially if there is no statistical interaction between the treatments[48].

In fact, we do not expect an interaction between the three interventions; that is, the effect of one intervention should not depend on the presence or absence of the other. But in the event that the efficacy of one intervention does depend on another (*e.g.*, steroids improve outcomes only if glucose is controlled), a factorial design will enable us to quantify the magnitude of the interaction. In contrast, this sort of interaction would be impossible to observe with three separate univariate trials. Factorial design is thus not only more efficient, but often superior to conventional trials that evaluate only a single intervention.

In our case, all three interventions are presumed to exert their protective effects through the same mechanism -- modulation of the peri-operative inflammatory response -- albeit possibly *via *different pathways. However, the putative effects of each are limited by a ceiling effect. Thus, a strength of the proposed factorial design is that we will be able to evaluate the presumed additive benefits of each intervention.

An added strength to our trial is that we will evaluate "hard" outcomes (major complications and mortality) rather than intermediate or indicator outcomes. Furthermore, the interventions we will test are fairly easy to use, inexpensive, and low-risk.

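### The sample size section says the study is powered for 40%, 20% and 10% reductions, but 970 patients power only the 40% effect; the 20% and 10% effects have about 30% and 10% power, and a true 20% reduction would usually be labelled futility

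*Protocol article*

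**What the plan says.** The article lists three primary hypotheses, one per intervention. Under Sample size considerations it takes a 25% event rate with no intervention ("We estimate that 25% of patients receiving no intervention (i.e., the control) will have at least one major complication") and then says the authors "will power the study for a relative reduction of 40% or more for at least one intervention, and 20% and 10% versus respective controls"; the last two figures belong to the remaining interventions. The next sentence gives the sample size, "a maximum of 970 total patients for the original group sequential portion of the study". The property it attaches to that number is "90% power at the 0.05 significance level to detect a 40% reduction on the primary outcome for the most promising intervention". No power is given for the 20% or 10% effect.

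The abstract shortens this to "We will enroll up to 970 patients which will provide 90% power to detect a 40% reduction in the primary outcome", and the Conclusion does much the same. Both keep the 40% but leave out that it refers to the most promising intervention.

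The interim monitoring section says that by the final analysis, counting a possible adaptive stage, "all of the interventions will have either crossed an efficacy or futility boundary". At the final look of the initial stage the two boundaries meet at p = 0.041, so every result is one or the other. The Figure 2 legend says the "inside shaded region indicates evidence to stop for futility, or no effect". Under Adaptive Design Option, a sample size extension may be proposed at the third look (N = 728) for an intervention with a modest effect that has crossed no boundary.

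**The concern.** Read as it stands, the sample size sentence puts all three effect sizes under the verb for powering. A design with 90% power for a 40% reduction cannot also have useful power for reductions half and a quarter as large, and the article does not say what power they have.

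The interpretation of two of the three primary hypotheses is at stake. If an intervention has the 20% benefit that the plan itself assumes, the likely outcome of the initial stage is futility, and the legend tells the reader that futility means no effect. Someone who had read that the study was powered for 20% would take such a result as evidence against a benefit of that size, which it would not be.

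**Working it through.** **Inputs.** From the article: 25% event rate with no intervention; relative reductions of 40%, 20% and 10%; maximum N = 970; two-sided 0.05; looks at 25%, 50%, 75% and 100%; gamma = −3 for efficacy and gamma = 0 for futility; printed p-values for efficacy (futility) of 0.003 (0.972), 0.007 (0.936), 0.017 (0.526) and 0.041 (0.041); main effects tested by collapsing over the other factors. Assumed: 1:1 allocation in each factor (485 per margin), multiplicative effects, no interaction, no extension.

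**Step 1: reproduce 970.** The marginal comparison rate for the 40% factor averages over the other two: 0.25 × (1 + 0.8)/2 × (1 + 0.9)/2 = 0.25 × 0.90 × 0.95 = 0.21375. With a 40% reduction the other arm is 0.21375 × 0.6 = 0.12825.
- The fixed-sample N for 90% power is about 804 (unpooled variance) or 812 (pooled).
- A four-look design with these spending functions and non-binding futility has efficacy p-values 0.003, 0.0071, 0.0173 and 0.0411, which match the printed ones, and an inflation factor of 1.214.
- 804.5 × 1.214 ≈ 977; 812 × 1.214 ≈ 986. Both are within 2% of 970.

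Comparing 25% with 15% directly gives only 804–813 in the same design. So 970 is reproduced when the 20% and 10% effects are used to set the marginal rate. That is the role they play in the calculation.

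**Step 2: drift of each factor at N = 970.** Drift = (p − q) / √{[p(1 − p) + q(1 − q)] / 485}. The design needs about 3.571 for 90% power.

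| Effect | p | q | Drift |
|---|---|---|---|
| 40% | 0.21375 | 0.12825 | 0.0855 / 0.02402 = 3.559 |
| 20% | 0.25 × 0.80 × 0.95 = 0.190 | 0.152 | 0.038 / 0.02415 = 1.574 |
| 10% | 0.25 × 0.80 × 0.90 = 0.180 | 0.162 | 0.018 / 0.02417 = 0.745 |

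**Step 3: put each drift through the four looks** (2 million simulated trials). The gamma = 0 calculation gave futility p-values of about 0.88, 0.52 and 0.16 at the three interim looks, not the printed 0.972, 0.936 and 0.526. The article does not state its software's convention, so the printed values are not called wrong, and results are shown for both sets (re-derived / printed).

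| True effect | Power | Ends in futility |
|---|---|---|
| 40% | 90% / 93% | 10% / 7% |
| 20% | 29% / 33% | 71% / 67% |
| 10% | 9% / 11% | 90% / 89% |

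**Step 4: sensitivity to the comparison rate.** With 25% as the comparison rate, power is 39–44% for the 20% effect and 12–14% for the 10% effect. A true 20% reduction ends in futility in 56–61% of trials.

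**Step 5: state at the third look for a true 20% effect.** Efficacy has been crossed in about 16–17% of trials and futility in 56% (re-derived) or 24% (printed). The remaining 28% or 60% are undecided and could be considered for the extension.

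**Scale.** In the same sequential design, 90% power at the marginal rates would need about 5,000 patients for the 20% effect and about 22,300 for the 10% effect.

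**The case against.** The strongest reply is that the sample size is right and the 20% and 10% figures were meant only as background. The calculation supports this, and the sentence that follows limits the 90% to the most promising intervention. A reader might infer that the plan claims 90% power for all three effects, or that 970 is wrong; the article supports neither. What remains is that the sentence does not call the smaller effects assumptions, and their power is nowhere given.

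Second, the adaptive option is aimed at modest effects, and the statement that every intervention reaches a boundary includes that stage. This stands: the 67–71% holds only if no extension is used. But the extension is optional and closed to an intervention that has already crossed futility, as a true 20% effect would have done by the third look in 24–56% of trials. It softens the low power without removing it. Nor is a 20% effect undetectable; its power is about 30%.

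Third, the futility rate is essentially one minus power, because any non-significant final result counts as futility. That is correct. It is the consequence of the low power, not a second fault.

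Fourth, a reader might infer that the 90% holds only if the other two effects are exactly 20% and 10%. That is not so: if they do nothing, the comparison is 25% with 15% and power for the 40% effect rises to 94–97%. Nor is the abstract's figure unqualified, since it is tied to a 40% reduction.

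Fifth, the Discussion says "the putative effects of each are limited by a ceiling effect", which might suggest that 90% is too high even for the best intervention. The article gives no size for the ceiling and says no interaction is expected. Any power figure under a ceiling, or with all three effects at 40%, would rest on the reader's own assumption, so none is part of this point.

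**Conclusion.** The point holds as a fault of wording and disclosure, not of sample size. The design supports the 90% claim for one 40% reduction (90–93%). It does not support saying that the study is powered for 20% and 10%: power for these is about 29–33% and 9–11% in the original stage at the marginal rates, or 39–44% and 12–14% at a 25% comparison rate. A true 20% reduction would be filed under the futility label in about 67–71% of trials, or 56–61% at 25%, if there is no extension. These figures assume 1:1 allocation, multiplicative effects and no interaction; the ranges cover the printed and the re-derived futility boundaries. On every variant the two smaller effects are clearly underpowered, and a futility crossing cannot be read as absence of a 20% effect.

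**What to change.** 1. **Sample size considerations:** say that 970 patients give 90% power for a 40% reduction for the most promising intervention only; that 20% and 10% are assumed effects of the other two, used to set the marginal event rate; and that their power before any adaptive extension is about 30% and 10%.
2. **Abstract and Conclusion:** add that the 90% refers to the most promising intervention, with a short note that smaller effects are not powered.
3. **Figure 2 legend:** replace the wording that equates futility with no effect by a statement that a 40% reduction is unlikely and that a reduction of 20% or less is not excluded.

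The cost is a few sentences and a less favourable-looking power statement. N, the boundaries and the analysis are unchanged.

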## Discussion

A factorial design will enable us to simultaneously study the effects of the three interventions; dexamethasone vs placebo, intraoperative tight vs. conventional glucose control, and light vs deep anesthesia, in the same population, both individually and in different combinations. Such a design is an economically efficient way to study the three interventions in one clinical trial vs three, especially if there is no statistical interaction between the treatments[48].

In fact, we do not expect an interaction between the three interventions; that is, the effect of one intervention should not depend on the presence or absence of the other. But in the event that the efficacy of one intervention does depend on another (*e.g.*, steroids improve outcomes only if glucose is controlled), a factorial design will enable us to quantify the magnitude of the interaction. In contrast, this sort of interaction would be impossible to observe with three separate univariate trials. Factorial design is thus not only more efficient, but often superior to conventional trials that evaluate only a single intervention.

In our case, all three interventions are presumed to exert their protective effects through the same mechanism -- modulation of the peri-operative inflammatory response -- albeit possibly *via *different pathways. However, the putative effects of each are limited by a ceiling effect. Thus, a strength of the proposed factorial design is that we will be able to evaluate the presumed additive benefits of each intervention.

An added strength to our trial is that we will evaluate "hard" outcomes (major complications and mortality) rather than intermediate or indicator outcomes. Furthermore, the interventions we will test are fairly easy to use, inexpensive, and low-risk.

### Limitations

The dose of steroids we have chosen may prove sub-optimal. Large-dose steroids have been shown to improve perioperative outcomes in patients undergoing cardiac or colorectal surgery[11,14]. However, concerns were raised about the possibility of theoretical side effects of such a large dose. Subsequent work by Kilger and associates suggests that much smaller doses are also effective,[15] and are -- presumably -- considerably safer. The anti-inflammatory potency of the dose we have chosen is comparable to that used by Kilger, although, we used dexamethasone rather than hydrocortisone[49]. It is also in line with the study by Bisgaard et al. that resulted in significantly lower CRP levels and improved recovery parameters. There was no increase in wound infection or other adverse outcomes[16]. Steroid administration will start 1-2 hours before surgery because the effects of steroids are believed to be mediated by protein synthesis which usually takes an hour or two[50].

Patients will be randomized to either a tight glucose control group with a goal of 80-110 mg·dl^-1 ^or to a conventional care group with a goal of 180-200 mg·dl^-1^. The lower range is that used by Van den Berghe et al, [28] and was shown to be beneficial in critical care patients. There were few complications associated with tight control in such a low range. The higher range essentially corresponds to current routine clinical practice. For example, a recent retrospective study showed that the rates of insulin treatment among academic anesthesiologists for glucose values < 140 mg·dl^-1^, 140-200 mg·dl^-1^, or > 200 mg·dl^-1 ^were 0.1%, 1.4%, and 11.9%, confirming that many anesthesiologists do not treat intraoperative glucose values less than 200 mg·dl^-1^[51].

Clinicians and study coordinators will be blinded to dexamethasone treatment. But due to the nature of the interventions, clinicians will not be blinded to the randomization regarding level of glucose control and depth of anesthesia in any given patient. The data collectors for postoperative events will be blinded to all three interventions.

### Conclusion

The DeLiT Trial is a multi-factorial randomized single-center trial of dexamethasone vs placebo, intraoperative tight vs. conventional glucose control, and light vs deep anesthesia in patients undergoing major non-cardiac surgery. The primary outcome is a composite of major post-operative morbidity including myocardial infarction, stroke, sepsis, and 30-day mortality. C-Reactive protein, a measure of the inflammatory response, will be evaluated as a secondary outcome. One-year all-cause mortality as well as post-operative delirium will be additional secondary outcomes. We will enroll up to 970 patients which will provide 90% power to detect a 40% reduction for the primary outcome, including three equally spaced interim analyses for efficacy and futility.

## List of abbreviations

ASA: American Society of Anesthesiologists; BIS: bispectral index; BUN: blood, urea, nitrogen; CAM: confusion assessment method; CDC: Center for Disease Control; CRP: C-Reactive protein; CT: Computed Tomography; CXR: chest x-ray; DIC: Disseminated Intravascular Coagulopathy; DVT: deep vein thrombosis; ECG: electrocardiogram; HCT: hematocrit; ICU: intensive care unit; LOS: length of stay; MAC: minimum alveolar concentration; PACU: postanesthesia care unit; POD: postoperative day; PONV: postoperative nausea and vomiting; RCT: Randomized Controlled Trial; Rx: Treatment; SF 12: health-related quality of life measure; TWA: time weighted average; VAS: visual analogue scale; VQ: Ventilation perfusion;
